**Table 2: Mean ( $\pm$  Standard Deviation) Pharmacokinetics Parameters of Free KL1333 in Study KL1333\_101**

|                                     | 25 mg
(N = 4)  | 50 mg
(N = 4)  | 100 mg
(N = 8)  | 200 mg
(N = 8)  | 400 mg
(N = 8)  | 600 mg
(N = 8) | 800 mg
(N = 8)  |
|-------------------------------------|---------------------------|---------------------------|----------------------------|----------------------------|----------------------------|---------------------------|----------------------------|
| $C_{\max}$
(ng/mL)               | 6.77
$\pm$ 6.39        | 7.59
$\pm$ 4.2         | 16.29
$\pm$ 7.62        | 24.68
$\pm$ 14.43       | 62.03
$\pm$ 11.74       | 119.4
$\pm$ 46.46      | 177.63
$\pm$ 61.7       |
| AUC 0-tlast
(ng.h/mL) | 24.06
$\pm$ 5.55       | 41.38
$\pm$ 13.79      | 104.71
$\pm$ 22.53      | 203.00
$\pm$ 39.78      | 471.92
$\pm$ 210.87     | 478.52
$\pm$ 101.00    | 723.28
$\pm$ 239.68     |
| AUC 0-∞
(ng.h/mL)     | 26.47
$\pm$ 6.51       | 53.60
$\pm$ 26.74      | 111.00
$\pm$ 24.79      | 205.99
$\pm$ 40.80      | 491.14
$\pm$ 213.05     | 477.71
$\pm$ 109.97    | 734.59
$\pm$ 234.43     |
| $V_z/F$ (L)                         | 18324.32
$\pm$ 6241.84 | 33780.5
$\pm$ 18982.24 | 44087.88
$\pm$ 37887.22 | 25300.59
$\pm$ 13461.38 | 41540.28
$\pm$ 30767.18 | 37750.88
$\pm$ 3829.53 | 55544.75
$\pm$ 51778.81 |
| CL/F
(L/h)                       | 999.35
$\pm$ 301.74    | 1122.1
$\pm$ 530.42    | 942.25
$\pm$ 218.13     | 1003.62
$\pm$ 191.41    | 961.78
$\pm$ 439.2      | 1320.42
$\pm$ 328.15   | 1190.8
$\pm$ 381.18     |
| $T_{\max}$ (h) a         | 1.25
(0.5 – 2)         | 1
(0.5 – 2)            | 1
(0.5 – 2)             | 2.01
(1 – 3)            | 2
(1 – 4.02)            | 2
(1 – 3)              | 2
(1 – 3)               |
| $t_{1/2}$ (h)                       | 13.73
$\pm$ 6.55       | 23.57
$\pm$ 14.11      | 34.64
$\pm$ 37.08       | 17.33
$\pm$ 7.68        | 33.98
$\pm$ 26.41       | 20.17
$\pm$ 7.21       | 31.23
$\pm$ 26.28       |

Abbreviations: AUC0-∞ = area under the plasma concentration-time curve from time zero to infinity; AUC0-tlast = area under the plasma concentration-time curve from time zero to the time of the last quantifiable concentration; CL/F = apparent total plasma clearance;  $C_{\max}$  = maximum observed plasma concentration;  $t_{1/2}$  = apparent plasma terminal elimination half-life;  $T_{\max}$  = time of the maximum observed plasma concentration;  $V_z/F$  = apparent volume of distribution during the terminal phase.

a Median (minimum-maximum).

**Table 3: Mean ( $\pm$  Standard Deviation) Pharmacokinetics Parameters of Total KL1333 in Study KL1333\_101**

|                               | 25 mg
(N = 4) | 50 mg
(N = 4) | 100 mg
(N = 8) | 200 mg
(N = 8) | 400 mg
(N = 8) | 600 mg
(N = 8)  | 800 mg
(N = 8)  |
|-------------------------------|--------------------------|--------------------------|---------------------------|---------------------------|---------------------------|----------------------------|----------------------------|
| $C_{max}$
(ng/mL)          | 294.60
$\pm$ 214.16   | 365.01
$\pm$ 125.96   | 980.18
$\pm$ 315.88    | 1385.12
$\pm$ 800.79   | 2977.67
$\pm$ 1111.25  | 5078.81
$\pm$ 2649.28   | 8247.30
$\pm$ 3354.44   |
| $AUC_{0-tlast}$
(ng.h/mL)  | 2503.93
$\pm$ 680.27  | 4090.94
$\pm$ 1223.35 | 9579.37
$\pm$ 1340.25  | 12860.68
$\pm$ 3460.51 | 21769.3
$\pm$ 6244.16  | 27173.77
$\pm$ 10359.42 | 38626.53
$\pm$ 9965.50  |
| $AUC_{0-\infty}$
(ng.h/mL) | 2978.21
$\pm$ 1045.48 | 5240.32
$\pm$ 2846.03 | 10130.97
$\pm$ 1735.47 | 13447.99
$\pm$ 3551.66 | 24593.09
$\pm$ 9440.25 | 28717.17
$\pm$ 10180.37 | 43220.35
$\pm$ 10461.06 |
| $V_z/F$ (L)                   | 301.30
$\pm$ 148.13   | 330.42
$\pm$ 83.86    | 351.79
$\pm$ 132.64    | 557.08
$\pm$ 314.47    | 864.38
$\pm$ 567.77    | 1122.91
$\pm$ 1046.53   | 1625.44
$\pm$ 1988.62   |
| CL/F
(L/h)                 | 9.48
$\pm$ 4.24       | 11.34
$\pm$ 4.64      | 10.11
$\pm$ 1.66       | 15.92
$\pm$ 4.75       | 18.47
$\pm$ 7.01       | 24.01
$\pm$ 10.62       | 19.62
$\pm$ 5.32        |
| $T_{max}$ (h) a    | 1.25
(0.5 – 2)        | 1
(0.5 – 2)           | 1
(0.5 – 2)            | 2.01
(1 – 3)           | 2
(1 – 4.02)           | 2
(1 – 3)               | 2
(1 – 3)               |
| $t_{1/2}$ (h)                 | 23.94
$\pm$ 13.79     | 24.95
$\pm$ 16.29     | 24.83
$\pm$ 10.61      | 24.21
$\pm$ 12.89      | 42.06
$\pm$ 46.79      | 33.82
$\pm$ 32.12       | 68.83
$\pm$ 103.18      |

Abbreviations:  $AUC_{0-\infty}$  = area under the plasma concentration-time curve from time zero to infinity;  $AUC_{0-tlast}$  = area under the plasma concentration-time curve from time zero to the time of the last quantifiable concentration; CL/F = apparent total plasma clearance;  $C_{max}$  = maximum observed plasma concentration;  $t_{1/2}$  = apparent plasma terminal elimination half-life;  $T_{max}$  = time of the maximum observed plasma concentration;  $V_z/F$  = apparent volume of distribution during the terminal phase.

a Median (minimum-maximum).

## 1.7. Study Rationale

KL1333 has been administered in a single ascending dose study in Korean subjects. The principal aim of this study is to obtain safety and tolerability data when KL1333 is administered orally as a single dose and as multiple doses to healthy, non-Korean subjects and as multiple doses to patients with mitochondrial disease. This information, together with the pharmacokinetic (PK) data, will help establish the doses and dosing regimen suitable for future studies in patients. The study will also investigate the effects of food on the PK of a single dose of KL1333 in healthy subjects prior to multiple-dose administration to confirm the dietary state for dosing. This study will also investigate the effect of KL1333 on biomarkers following multiple doses in healthy subjects and patients with mitochondrial disease and the effect of KL1333 on clinician- and patient-rated outcome assessments following multiple doses in patients with mitochondrial disease.

## 1.8. Benefit-risk Assessment

Healthy subjects in the current study will not receive any health benefit (beyond that of an assessment of their medical status) from participating in the study.

The patients with mitochondrial disease randomised to active treatment might clinically benefit from receiving multiple doses of a potential new treatment for their disease. It is possible that by participating in this study the condition of the patients with mitochondrial disease could possibly temporarily improve, but this cannot be guaranteed.

The risks of participation are primarily those associated with adverse reactions to the investigational medicinal product (IMP), although there may also be some discomfort from collection of blood samples and other study procedures. More information about the known

and expected benefits, risks, and reasonably anticipated AEs associated with KL1333 may be found in the Investigator's Brochure (IB).

## **2. OBJECTIVES AND ENDPOINTS**

### **2.1. Objectives**

The primary objectives of the study are:

- To evaluate the safety and tolerability of a single oral dose, with and without food, and multiple ascending oral doses of KL1333 in healthy subjects
- To evaluate the safety and tolerability of multiple oral doses of KL1333 in patients with mitochondrial disease.

The secondary objectives of the study are:

- To determine the single oral dose plasma PK of KL1333 in healthy subjects, including the effect of food intake
- To determine the multiple oral dose plasma PK of KL1333 in healthy subjects and patients with mitochondrial disease.

The exploratory objectives of the study are:

- To explore the multiple-dose pharmacodynamics (PD) of KL1333 in healthy subjects and patients with mitochondrial disease using blood biomarkers
- To explore clinician- and patient-rated outcome assessments following multiple oral doses of KL1333 in patients with mitochondrial disease
- To collect blood samples for analysis of metabolomics following multiple oral doses of KL1333 in healthy subjects and patients with mitochondrial disease
- To assess the effect of KL1333 on ECG parameters, including concentration-QT interval corrected for HR (QTc) analysis, in healthy subjects
- To collect blood samples for NQO1 genotyping from healthy subjects who receive single or multiple oral doses of KL1333 and patients with mitochondrial disease who receive multiple oral doses of KL1333.

### **2.2. Endpoints**

#### **2.2.1. Primary Endpoints**

The primary safety endpoints for this study are as follows:

- incidence and severity of AEs
- incidence of laboratory abnormalities, based on haematology, clinical chemistry, and urinalysis test results
- 12-lead ECG parameters

- vital signs measurements
- physical examinations.

### 2.2.2. Secondary Endpoints

For Part A, the single-dose and food-effect (fed versus fasted dietary status at dosing) PK outcome endpoints of KL1333 are as follows:

- AUC from time zero to infinity ( $AUC_{0-\infty}$ )
- $AUC_{0-24}$
- AUC from time zero to the time of the last quantifiable concentration ( $AUC_{0-t_{last}}$ )
- $C_{max}$
- time of the  $C_{max}$  ( $T_{max}$ )
- apparent plasma terminal elimination half-life ( $t_{1/2}$ )
- mean residence time (MRT)
- apparent total plasma clearance (CL/F)
- apparent volume of distribution during the terminal phase ( $V_z/F$ ).

For Parts B through D, the multiple-dose PK outcome endpoints of KL1333 are as follows:

- $AUC_{0-\infty}$  (Day 1 only)
- AUC over a dosing interval ( $AUC_{0-\tau}$ ; Days 1 and 10)
- temporal change parameter (TCP;  $AUC_{0-\tau}/AUC_{0-\infty}$ )
- $C_{max}$
- minimum observed plasma concentration ( $C_{min}$ )
- $T_{max}$
- $t_{1/2}$
- MRT on Days 1 and 10
- CL/F on Days 1 and 10
- $V_z/F$  on Days 1 and 10
- observed accumulation ratio based on  $AUC_{0-\tau}$  ( $RA_{AUC}$ )
- observed accumulation ratio based on  $C_{max}$  ( $RA_{C_{max}}$ )
- peak-to-trough ratio (PTR).

Other PK parameters may also be calculated if appropriate.

### 2.2.3. Exploratory Endpoints

For Parts B through D, the multiple-dose PD outcome endpoints are as follows:

- NAD+/NADH concentrations and ratio
- FGF21
- GDF15
- lactate/pyruvate concentrations and ratio.

For Part C, the multiple-dose PD outcome endpoints will also include:

- glucose
- glycated albumin/albumin concentrations and ratio.

For Part C, the clinician- and patient-rated outcome endpoints are as follows:

- Newcastle Mitochondrial Disease Adult Scale (NMDAS)
- Clinician Global Impression (CGI)
- Patient Global Impression-Improvement (PGI-I)
- Daily Fatigue Impact Severity (D-FIS)
- Quality of Life in Neurological Disorders Fatigue (Neuro-QoL Fatigue) Short Form
- 30 Second Sit-to-Stand Test.

For Parts A and B, continuous ECGs will be collected, and endpoints for the continuous ECG evaluation will include:

- change from baseline ( $\Delta$ ) HR and QTcF, PR, and QRS intervals ( $\Delta$ HR,  $\Delta$ QTcF,  $\Delta$ PR, and  $\Delta$ QRS)
- placebo-corrected change from baseline ( $\Delta\Delta$ ) in  $\Delta$ HR,  $\Delta$ QTcF,  $\Delta$ PR, and  $\Delta$ QRS ( $\Delta\Delta$ HR,  $\Delta\Delta$ QTcF,  $\Delta\Delta$ PR, and  $\Delta\Delta$ QRS)
- categorical outliers for HR and QTcF, PR, and QRS intervals
- frequency of treatment-emergent changes of T-wave morphology and U-wave presence.

### 3. INVESTIGATIONAL PLAN

This will be a double-blind, randomised, placebo-controlled, single and multiple oral dose study conducted in 4 parts. An overview of the planned dose levels for all parts of the study is shown in [Figure 2](#).

**Figure 1: Study Dose Levels**

Part A-Healthy Subjects

[figure not shown]

Part B-Healthy Subjects

[figure not shown]

Part C-Mitochondrial Disease Patients

[figure not shown]

Part D-Healthy Subjects

Group D1  
75 mg (N = 6)  
Placebo (N = 2)  
Twice daily for  
10 days

Group D2  
50 mg (N = 6)  
Placebo (N = 2)  
Three times  
daily for 10 days

Note: Additional single-dose cohorts Groups A2 and A3 may be enrolled based on data obtained from either Parts A or B. If needed, dose level and dietary state will be determined from review of data in Part A and available data from Part B.

For Part B, dose levels, dose frequency, and dietary state will be confirmed from review of data in Part A and available data from Part B.

For Part C, dose levels, dose frequency, and dietary state will be confirmed following review of data from Part B, and unless deemed very unfavourable for the conduct of the study, the patients will not be required to be fasting prior to dosing.

For Part D, subjects will be fasted for the first dose on Day 1 and single dose on Day 10 for intensive pharmacokinetic sampling and the first dose on Day 7 for clinical laboratory evaluations. All other doses may be given without regard to food.

### 3.1. Overall Study Design and Plan

#### 3.1.1. Part A

Part A will comprise a randomised, single-dose, single-sequence, placebo-controlled study. Eight healthy subjects will be studied in a single cohort (Group A1).

Potential subjects will be screened to assess their eligibility to enter the study within 28 days prior to the first dose administration. Subjects will participate in 2 treatment periods. For each treatment period, subjects will reside at the Phase I clinical site from Days -1 to 3 (48 hours postdose). Subjects will return to the clinical site for outpatient visits on Days 4 and 5. There will be at least a 10-day washout between doses (from Period 1, Day 1 to Period 2, Day 1).

Six subjects will be randomised to receive 25 mg KL1333 and 2 subjects will be randomised to receive placebo, and subjects will receive the same treatment in both treatment periods. On Treatment Period 1, Day 1, subjects will receive a single oral dose of study drug following an overnight fast of at least 8 hours. On Treatment Period 2, Day 1, subjects will receive a single oral dose of study drug after consuming a standard high-fat breakfast. Following review of safety, tolerability, and PK data, up to 2 additional dose cohorts of healthy subjects may be added if needed to determine the study treatment for Part B. Additional single-dose cohorts may be enrolled based on data obtained from either Parts A or B. If additional cohorts are required, each cohort will consist of 8 subjects, with 6 subjects receiving KL1333 and 2 subjects receiving placebo, and will undergo a single treatment period. The dose level and dietary state for administration of KL1333 in these potential additional cohorts will be decided following review of data in Part A and any available data from Part B, and the dose level could be either less than or greater than 25 mg. The dose level will not exceed 600 mg,

and the predicted exposure following a single dose in any subject in Part A will not exceed an  $AUC_{0-24}$  of 51,800 ng.h/mL for derived total KL1333.

Subjects will return for a Follow-up visit on Day 6, 5 days after their final dose.

An overview of the study design is shown in [Figure 2](#).

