| Check-out                             |                               |                                        | Day 3                                                                                                |                                |                      |                       |
| Nonresidential visit                  | X                             |                                        |                                                                                                      | X                              | X                    | X                     |
| Study drug
administration: |                               |                                        |                                                                                                      |                                |                      |                       |
| KL1333 or placebo                     |                               |                                        | Day 1 (0 hour; 30 minutes after starting a high-fat
breakfast in Treatment Period 2) f |                                |                      |                       |
| Pharmacokinetics:              |                               |                                        |                                                                                                      |                                |                      |                       |
| Blood sampling                        |                               |                                        | Predose and 0.25, 0.5, 1, 2, 3, 4, 6, 8, 10, 12, 24, 36, and
48 hours postdose                    | 72 and
96 hours
postdose | X                    | 120 hours
postdose |

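### In the Group A1 food-effect comparison, fasted sampling stops at 96 h and fed sampling at 120 h, so the schedule alone can inflate the fed/fasted AUC0-tlast ratio (minor)

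*Protocol*

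**What the plan says.** Protocol Section 3.1.1 describes the design: "Part A will comprise a randomised, single-dose, single-sequence, placebo-controlled study". The order of dietary states is fixed. For the fasted dose: "On Treatment Period 1, Day 1, subjects will receive a single oral dose of study drug following an overnight fast of at least 8 hours". For the fed dose: "On Treatment Period 2, Day 1, subjects will receive a single oral dose of study drug after consuming a standard high-fat breakfast".

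After discharge in each period, "Subjects will return to the clinical site for outpatient visits on Days 4 and 5". Then: "Subjects will return for a Follow-up visit on Day 6, 5 days after their final dose".

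Appendix 5, Table 1 (Part A) matches this. The heading for Treatment Periods 1 and 2 covers Day -1, Days 1 to 3, and Days 4 and 5. The last PK samples under it are "72 and 96 hours postdose". The sample at "120 hours postdose" appears only in the separate Follow-up column.

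Section 2.2.2 opens the Part A list with the single-dose and "food-effect (fed versus fasted dietary status at dosing) PK outcome endpoints of KL1333 are as follows". The list contains AUC0-∞, AUC0-24, AUC0-tlast, Cmax, Tmax, t1/2, MRT, CL/F and Vz/F. Section 8.3 says the food effect will be examined by ANOVA. It does not name the parameters that enter the model and sets no common end time.

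**The concern.** AUC0-tlast is a property of the sampling schedule as well as of the drug. Where concentrations remain measurable, a later last sample gives a larger AUC0-tlast. In A1 the longer window always goes with the fed dose. Window, period and dietary state are therefore fully confounded, and no term in the ANOVA can separate them. An error of this kind has a fixed direction and does not shrink with more subjects.

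Section 3.4 justifies the crossover as a within-subject assessment of the influence of food. That presumes the two conditions are observed alike. What is at stake is the accuracy of one reported food-effect estimate.

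**Working it through.** **Inputs.** Protocol Table 3 (total KL1333, 25 mg, earlier assay, earlier study) gives t1/2 23.94 h (SD 13.79), Vz/F 301.30 L, CL/F 9.48 L/h, AUC0-tlast 2503.93 and AUC0-∞ 2978.21 ng.h/mL. The half-lives examined are the mean and the mean ± 1 SD: 10.15, 23.94 and 37.73 h. The assay limit (LLOQ) is not given; 0 to 10 ng/mL is assumed.

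**The plan's own figures.** Section 3.6 treats 48 h as about 2 half-lives and 5 days as about 5. These reproduce: 48/23.94 = 2.01 and 120/23.94 = 5.01. The fasted profile ends at 96/23.94 = 4.01 half-lives. As a cross-check, ln 2 × 301.30/9.48 = 22.0 h.

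**Effect on AUC0-tlast with no food effect.** Let f be the share of AUC that lies in the terminal phase (assumed 0.5 to 1; f = 1 is a one-compartment profile). Then

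ratio = (1 − f × 0.5^(120/t1/2)) / (1 − f × 0.5^(96/t1/2))

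| t1/2 (h) | AUC beyond 96 h (f = 1) | AUC beyond 120 h (f = 1) | Ratio, f = 1 | Ratio, f = 0.5 |
|---|---|---|---|---|
| 10.15 | 0.14% | 0.03% | 1.001 | 1.001 |
| 23.94 | 6.21% | 3.10% | 0.9690/0.9379 = 1.033 | 1.016 |
| 37.73 | 17.14% | 11.03% | 0.8897/0.8286 = 1.074 | 1.033 |

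Two-compartment profiles matched to the 25 mg Cmax and AUC0-∞ of Table 3 gave 1.015–1.027 at 23.94 h and 1.030–1.056 at 37.73 h. They supply the lower ends of the quoted ranges.

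**Dependence on the LLOQ.** With a one-compartment starting level of 25,000/301.3 = 83.0 ng/mL, the expected concentrations are 5.1 ng/mL at 96 h and 2.6 at 120 h for a half-life of 23.94 h, and 14.2 and 9.2 for 37.73 h. A noncompartmental analysis was simulated with 3,000 runs per case, an assumed 20% residual CV, the linear trapezoid and a log-linear terminal fit from 24 h. The 120-h versus 96-h AUC0-tlast ratios were:

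| Profile | LLOQ 0 | LLOQ 1 | LLOQ 5 | LLOQ 10 |
|---|---|---|---|---|
| One-phase, 23.94 h | 1.038 | 1.038 | 1.000 | 1.000 |
| Two-phase, 23.94 h | 1.022 | 1.019 | 1.002 | 1.000 |
| One-phase, 37.73 h | 1.074 | 1.077 | 1.076 | 1.029 |
| Two-phase, 37.73 h | 1.049 | 1.049 | 1.032 | 1.001 |

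**Terminal-phase parameters.** In the same simulation with a log-linear tail and an LLOQ of 0 to 1 ng/mL, the t1/2 ratio was 0.99–1.01 and the AUC0-∞ ratio 0.99–1.00. At an LLOQ of 5 to 10 ng/mL, t1/2 ran from 0.985 to 1.036 and AUC0-∞ from 0.994 to 1.015, with no consistent direction. Only a deliberately curved tail (phases of 15 h and 45 h, LLOQ 0 to 1) moved t1/2 clearly, by about 8%. AUC0-∞ then moved by at most about 1%.

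**The case against.** The schedule difference itself cannot be disputed. The case against making much of it is strong on four points.

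*It may not arise.* The LLOQ is unknown. In Table 3 at 25 mg the extrapolated part is 2978.21 − 2503.93 = 474 ng.h/mL. At 23.94 h that implies a last concentration of about 474 × 0.693/23.94 = 14 ng/mL (a ratio of means, so approximate), which is above the 96-h level predicted here. Whether the earlier study stopped there because of its assay or its schedule cannot be told. Section 3.5 expects the revised assay to report higher values, which makes quantifiable late samples more likely but does not settle it. This stands: the inflation is conditional, and a reader should not infer that it always raises the fed result.

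*It is small beside the noise.* With 6 active subjects and an assumed within-subject CV of 20%, the log-scale SE is 0.198 × √(2/6) = 0.114. The 90% interval is then exp(± 2.015 × 0.114), or about 0.79 to 1.26 around a ratio of 1. The protocol sets no food-effect limits. This stands as to size, but imprecision does not remove a systematic error.

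*It drives no stated decision.* A reader might infer that the dietary state of later cohorts hangs on this ratio. The documents do not support that. Dietary state follows a joint review of safety, tolerability and PK (Section 3.1.2), and the exposure cap is AUC0-24 (Section 3.7), which is untouched. Section 3.4 reports Part B complete, Part D's conditions are fixed, and Part C's are to be confirmed from Part B data. Optional extra Part A cohorts remain in the text, but nothing ties them to AUC0-tlast.

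*It is a matter for the SAP.* A common end time is indeed a routine analysis specification, and Section 7.1.1 allows up to 3 extra PK samples per period. But the protocol itself fixes the unequal schedules and names a window-dependent endpoint for the comparison, and it plans no 120-h sample after the fasted dose. Followed as written, it produces the confounded ratio. This objection does not dispose of the point.

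**Conclusion.** The point holds for AUC0-tlast and is minor. If concentrations remain quantifiable at 120 h, the schedule alone inflates the fed/fasted ratio by about 1.5–3.3% at the documented mean half-life and 3–7% at the mean plus 1 SD. The effect is about nil at a half-life of 10 h, or when the LLOQ removes the late samples. These figures rest on earlier-study, earlier-assay PK values, on the assumed terminal share of AUC, and on an assumed LLOQ.

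A reader might also infer that half-life, AUC0-∞, MRT and Vz/F are biased. That is not shown. With a log-linear tail the extra sample changes precision and the extrapolated fraction, not the expected value; bias would need a curved tail or censoring at the LLOQ. What can be said is that these parameters are estimated from unequal windows. Cmax and AUC0-24 are unaffected.

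**What to change.** In the food-effect comparison, replace AUC0-tlast with AUC over a window common to both periods: AUC0-96 or, where the 96-h sample is not quantifiable, AUC to the last time quantifiable in both periods within the subject. With equal windows the schedule-induced ratio is 1.00.

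Keep AUC0-∞, t1/2, MRT and Vz/F on all available data, and add a sensitivity analysis with Period 2 truncated at 96 h. Truncation should not be the main analysis of these parameters, because it would raise the extrapolated share of the fed AUC from 3.1% to 6.2% at 23.94 h (one-compartment) to cure a bias that has not been shown. Retain the 120-h sample for the descriptive Period 2 profile and its AUC0-tlast.

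The cost is a sentence or two in the PK analysis section or the SAP. No new visit or sample is needed, and the change applies to data already collected. The downside is that one late fed sample goes unused in that one comparison.
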